## Abstract

**Background:**

Many children would benefit from a diet richer in vegetables and fruit. ‘Flavour School’ is a programme of ‘sensory food education’, which aims to increase children’s confidence and curiosity in exploring foods and flavours, especially vegetables and fruit. This study will conduct a cluster-randomised controlled trial to assess the outcomes of the Flavour School programme in primary school children aged 4–7 years.

**Methods:**

Four hundred plus children from 4+ schools will either complete the Flavour School programme (experimental group) or have no intervention with normal school teaching (control group), cluster-randomised within-schools, by school class. Baseline data collection will consist of video recorded behavioural observation during a tasting activity, and post-intervention data collection will repeat this activity after the experimental group have completed the intervention. Process measures will be assessed using a teacher engagement feedback questionnaire.

**Discussion:**

This study will provide causal data on the efficacy of a sensory food education intervention for increasing children’s confidence and curiosity in exploring foods and flavours, especially vegetables and fruit. This new knowledge will help educators and policy makers to make evidence based decisions on uptake of sensory food education.

**Trial registration:**

ISRCTN: 40249947 Date assigned 17 March 2020 Last edited 22 September 2021 Version 1.2

Trial Acronym OASES (Outcomes Assessment of Sensory Education in Schools)

**Supplementary Information:**

The online version contains supplementary material available at 10.1186/s13063-022-06612-2.

## Administrative information

Note: the numbers in curly brackets in this protocol refer to SPIRIT checklist item numbers. The order of the items has been modified to group similar items (see http://www.equator-network.org/reporting-guidelines/spirit-2013-statement-defining-standard-protocol-items-for-clinical-trials/).

## Introduction

### Background and rationale {6a}

The World Health Organization (WHO) rates diet related disease as a principle health burden in Europe [1]. Obesity and its co-morbidities, type 2 diabetes, and common cancers are amongst the greatest concerns [2, 3]. Eating disorders are also on the rise [4]. A healthy diet is associated with good physical and mental health [5]. Food insecurity and dietary inequalities are also important issues in the UK and are strongly linked to poverty and wider inequalities [6]. Diet in childhood tracks to diet in adulthood, emphasising the importance of early intervention [7–9].

One key area of concern highlighted by the WHO is low consumption of vegetables and fruit, especially vegetables. Most people do not eat the recommended minimum of 400g per day [10, 11]. Early life intake of a sufficient variety and quantity of vegetables and fruit (henceforth ‘FV’) provides access to a wide range of health-protective micronutrients and phytonutrients [12]. A FV rich diet containing at least five 80 g portions per day (for adults) is recommended by the UK National Health Service.^1^ Strong epidemiological evidence suggests that a diet rich in FV decreases risks for many health conditions including type 2 diabetes, cardiovascular disease, hypertension, stroke and some cancers [13, 14].

In the UK, children consume on average about 2.5 portions per day (half the recommended 5 portions), and many children obtain a large proportion of their energy intake from energy dense snack foods [15]. Increasing plant-based foods as a proportion of dietary intake is also widely accepted as one crucial aspect of a shift to ecologically sustainable food systems [16].

### Increasing children’s fruit and vegetable consumption

Changing children’s eating habits is challenging. Broadly speaking, trials of interventions intended to increase FV consumption have mostly shown statistically significant, but small, changes in consumption, and there is an increasing consensus that multiple systemic issues will need to be addressed concurrently to make a large impact on children’s FV consumption and wider dietary health, especially amongst the children most in need [17–20]. Preference consistently ranks amongst the top perceived barriers to FV consumption, especially for vegetables [11, 21, 22]. Repeated taste exposure is the best evidenced method for increasing liking in children [19, 23]. Non-food rewards can help, primarily by convincing children to actually taste many times [24]. Incorporating non-food tangible rewards such as stickers, alongside peer modelling and repeated tasting, in the multicomponent school intervention ‘Food Dudes’ had encouraging outcomes in increasing tasting, liking and consumption of FV [25, 26].

The development of healthy dietary variety via repeated taste exposure may be weakened by individual child eating traits such as food ‘neophobia’ (suspicion of novel foods) and ‘fussiness’ (very selective eating), which affect many young children to varying degrees, especially between 2 and 5 years of age [27–29]. Many exposures may be needed to change preferences, and exposure effects may be specific to the target vegetable [30]. Especially with younger children, it can be difficult and frustrating to persuade a reluctant child to repeatedly taste disliked foods.

Multisensory approaches could offer a less combative route to familiarisation for pre-school age children [30]. Acceptance of (initially) unfamiliar vegetables can increase with hands-on non-tasting sensory sessions in children aged 1–3 years [31] and 3–4 years [32, 33], and picture books can boost effects of sensory activities [34]. Non-taste multisensory play activities may be especially useful for neophobic or selective eaters, in providing a less threatening route to familiarisation than repeated tasting [35].

‘Sensory food education’ is a more structured approach than sensory play, originating in the ‘*Classes du goût*’ programme devised by French sensory scientist Jacques Puisais [36]. In 8–12 year old children, small improvements in willingness-to-taste have been reported [37, 38], alongside improvements in sensory discrimination and description [39], and development of preferences for more complex flavours [40]. Across these four studies, statistical significance was driven by the younger participants, and no effect on willingness-to-taste was found in Dutch school children aged 9-11 [41], suggesting that sensory food education may be most effective for younger children. In 3–6 year old Finnish children [42], and [43] both reported small but significant improvements in willingness to taste and consume FV.

In summary, as a recent review of children's food education concludes [20], despite some encouraging results, studies have mostly been either small, or based on surveys, and/or unrandomised, and so the purported benefits of ‘*Classes du goût*’ style sensory food education in schools remain to be clearly and causally demonstrated in larger behavioural outcome observation experiments and randomised controlled trials (RCTs). The OASES study will provide the first RCT of a *Classes du goût* style sensory food education intervention in the target age group (4–7 year old children) [44]. Details the study protocols for a randomised control trial of outcomes for a multi-component intervention featuring sensory food education, in Norwegian nursery children aged 1–3 years. Quantitative results of this study are not yet published at time of submission.

### Objectives {7}

The primary objective is to assess the effectiveness of the Flavour School sensory food education programme, with respect to its stated aim of “growing children’s confidence and curiosity in exploring (healthy) foods and flavours, especially vegetables and fruit”. A secondary objective is to assess the validity of automated video coding using the Noldus FaceReader, relative to trained human video coders, in our experimental context.

### Trial design {8}

The OASES trial is designed as a cluster-randomised, controlled, superiority, parallel group two-arm cohort study, with before and after observations, and pragmatic blinding (see {17a}). Outcomes measurement will focus on video recorded behavioural observation of children engaging in a tasting activity (following [45]).

## Methods: participants, interventions and outcomes

### Study setting {9}

The intervention and data collection will take place in primary schools in Greater London and Leeds, UK. Participating schools are (in Leeds) are Summerfield Primary, Swinnow Primary, Carr Manor Primary. In London, St Mary’s Catholic Primary (Hornchurch) and Woodmansterne Primary (Streatham).

### Eligibility criteria {10}

#### School inclusion/exclusion criteria

Participation is open to primary schools in London and Leeds regions, for children in reception, year 1 and year 2 (age range 4–7 years). Schools decide which of these year groups will participate in the study. Special needs schools, independent schools and very small schools (less than one class group per year group) will not be included.

#### Individual inclusion criteria

All children in experimental group classes will receive the intervention, delivered as part of regular school teaching. Children in the control group will receive normal teaching with no intervention. No particular level of spoken English is required. However, only children with opt-in caregiver consent will contribute data to the study.

### Who will take informed consent? {26a}

There will be two routes for caregiver consent for participating children. An online route will direct caregivers to a dedicated page at onlinesurveys.ac.uk, where they will receive information about the study, and can give consent for their child’s participation. However, pilots showed that many caregivers do not engage in the online route, so there will also be an in-person, on-paper consent route run by teachers in participating classes.

### Additional consent provisions for collection and use of participant data and biological specimens {26b}

Caregivers can opt-in to allow the use of their child’s video data for communications about the intervention and the study. Their child can participate regardless of this consent being giving. This trial does not involve collecting biological specimens.

### Interventions

#### Explanation for the choice of comparators {6b}

The comparator condition is normal teaching with no intervention. Though there might be advantages to an active intervention comparator, the burden on schools would be increased, making recruitment difficult. The real-world comparator is likely to be schools deciding whether to alter their normal teaching to include the intervention, so this comparator should provide a good reflection of real-world decision making context.

#### Intervention description {11a}

Flavour School is a programme of sensory food education, aimed at primary school children aged 4–7 years. Children participate in sensory activities with food (mostly FV), to learn about how their various senses contribute to their eating experiences, whilst familiarising and ‘making friends’ with healthy foods. Children also learn conversation skills and vocabulary to describe and share their sensory experiences. The programme is delivered once-weekly over one school term. Prior to the intervention, participating teachers attend a teacher training session and are provided with teaching materials. Flavour School aims to ‘grow children's curiosity and confidence in exploring foods and flavours, to support the development of healthy, happy relationships with food’. The Flavour School programme is produced and supported by the charity Flavour School (#1178084).

#### Criteria for discontinuing or modifying allocated interventions {11b}

There will be no special criteria for discontinuing or modifying allocated interventions.

#### Strategies to improve adherence to interventions {11c}

Researchers will keep in contact with participating schools and teachers throughout the trial, to ensure intervention delivery is progressing as planned, and offer support where needed.

#### Relevant concomitant care permitted or prohibited during the trial {11d}

There are no restrictions regarding concomitant care during the trial. However, schools will be instructed not to deliver any other sensory food education programmes to participating classes during the trial.

#### Provisions for post-trial care {30}

There is no anticipated risk of harm and compensation for trial participation.

### Outcomes {12}

The observational scenario is a tasting activity done in small groups (see the “Plans for assessment and collection of outcomes {18a}” section). The test activity will conducted < 6 weeks before (baseline) and < 6 weeks after intervention delivery is completed. Analysis metric for all measures is follow-up scores, adjusted for baseline, for all children.

### Primary measures

‘Curiosity and confidence’ are operationalised in terms of the following observable proxy behaviours.Willingness to taste novel and familiar vegetables, legumes and fruit (supervised self-report)Non-verbal ‘Enjoyment and Engagement’ (from observation of children’s facial expressions)Verbal engagement (child’s speaking time and sensory vocabulary during the activity)Normalised linear combination (mean) of 1, 2 and 3 as an overall measure of ‘curiosity and confidence’ in tasting

### Validation of Noldus FaceReader

In our experimental context, is the Noldus FaceReader software sufficiently accurate to partially replace human observers?

### Exploratory analysis

Liking for the offered range of foods (self-report)

### Primary measures

Children are not experimentally observed during the delivery of the intervention. All evaluation data are collected during the baseline and follow-up evaluation sessions, administered and supervised by the experimenter, before and after the intervention. See Additional file 1: Appendix 2 for more details of the coding regime for annotation of the video data.

### Willingness-to-taste (WTT)

Children are offered nine plant foods (see Additional file 1: Appendix 1 for list of foods), in a compartmentalised tray. ‘Self-reported WTT’ is simply the proportion of these that a child tastes, as indicated by the faces they draw on their My Tasting Card (see Fig. 2).

Children are instructed that nibbling and licking are included as tasting. A child who eats all of every sample therefore has the same self-reported WTT score as a child who takes tiny nibbles of all samples, though their behaviours are notably different. To finesse WTT scores such that these differences are noted, the human observers coding the video footage will also produce a ‘Gusto’ rating to summarise how enthusiastically each child tastes/eats the food samples, rating from 1 (very unenthusiastic) to 5 (very enthusiastic). These Gusto ratings will be used to weight the self-reported WTT scores (i.e. WTT = self-report WTT * Gusto). We will report both self-report WTT and WTT.

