### Exploratory analysis

#### Liking for the food samples (this is an exploratory analysis)

During the Flavour Explorers tasting activity, the children draw ‘emoji style’ faces to indicate their liking for the food samples they taste (see the “Plans for assessment and collection of outcomes {18a}” section for more details). The primary purposes of this are (a) to serve as supervised self-report of willingness-to-taste and (b) to give the data collection scenario the feel of an ‘activity’, rather than the feel of a ‘test’.

The children have quite a lot of freedom in the faces they draw, and some children (especially the younger ones) are still mastering use of a pen. In pilots, the faces children drew were not always decipherable. As a result, the liking measure is likely to be rather noisy, with limited coverage, especially for children in reception class (i.e. the youngest children). There is no particular reason to anticipate significant pre-post changes in liking. Nonetheless, given we will have some data on children’s liking for the samples, it makes sense to explore this data, noisy as it may be. For these reasons, we will examine Liking as a secondary measure, and an exploratory analysis.

Liking will be calculated as the sum of all the faces drawn on a child’s My Tasting Card, where each face type is rated as follows:‘frowny’ face = 0‘flat’ face = 1‘smiley’ face = 2

Liking will use the same statistical analysis used for the primary measures (see the “Statistical methods for primary and secondary outcomes {20a}” and “Methods for additional analyses (e.g. subgroup analyses) {20b}” sections). We will also calculate correlation between liking and WTT, as we are interested in the extent to which WTT depends on like/dislike for the foods offered.

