### Assignment of interventions: blinding

#### Who will be blinded {17a}

Data analysts/video coders will be blind to condition (control/intervention) and time point (pre- or post-intervention) of a given video and participant under analysis. Due to the experiential nature of the intervention, it is not possible to blind the study participants (children and teachers) to their condition (control/intervention). The lead researcher, who will conduct data collection, will be pragmatically blinded to which classes/clusters are in which condition. However, this blinding is imperfect due to contact between the lead researcher and participants during data collection (e.g. a child might talk about doing Flavour School activities, revealing that their class is in the intervention group).

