**Fig. 2 Fig2:**
[figure not shown]
**a** Each child has a selection of FV in a compartmentalised tray. Children are free to taste (or not) any of the items, in any order. **b** Children record their tasting with an ‘emoji’ drawing to indicate like/neutral/dislike. Untasted items are left blank (e.g. blue circle). The testing table. Up to 4 chidlren participate together, each with their own tray of food samples. Located centrally on the table is a dedicated camera for each child

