#### Plans for assessment and collection of outcomes {18a}

Behavioural data collection is conducted through a tasting activity we call ‘Flavour Explorers’. The activity itself is individual, but is performed in a peer-group of three or four to enable conversation and make the scenario comfortable for the children participating. The children are supervised by the researcher(s). The children sit on cushions on the floor, around a small circular table.

Each child is provided a small tray with nine compartments, each containing one food sample. Each compartment/food sample is marked with a different colour dot sticker. Each child is also provided a ‘My Tasting Card’, with nine colour blobs matching the food samples/compartments. When a child tries a food, they use ‘emoji’ style drawings to note their liking for the food (sad face, neutral face, or happy face) on their Card. See Fig. 2. Children are given as much time as they need (within reason), and sessions typically last between 8 and 12 min.

The sample consist of seven vegetables (including a legume and a herb), and two fruits, and include both common/familiar and obscure/unfamiliar produce. Different food sample sets will be used for pre- and post-intervention testing, counterbalanced at random by school class group. See Additional file 1: Appendix 1 for more details.

Flavour Explorers sessions will be video recorded, with an individual video stream for each child. A dedicated Yi4k+ action camera for each child is located in the centre of the table. The My Tasting Cards provide the raw data for analysis of willingness-to-taste (WTT) and liking, whilst video/audio provides raw data for affect from facial expression, and verbal engagement (Fig. 3).

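### Primary willingness-to-taste is counted only from cards marked by unblinded children, so a change in marking could be read as a change in tasting; a blinded video count would check it

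*Protocol article*

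**What the plan says.** The list under Primary measures opens with "Willingness to taste novel and familiar vegetables, legumes and fruit (supervised self-report"). The section Willingness-to-taste (WTT) says that the self-reported score "is simply the proportion of these that a child tastes, as indicated by the faces they draw on their My Tasting Card". Nine foods are offered, and the caption of Fig. 2 gives the rule for the rest: "Untasted items are left blank". Section {18a} names the cards as raw data for WTT and liking, and gives facial affect and verbal engagement to the video and audio. Section {17b} has the lead researcher score WTT from the cards, before being told the allocation.

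On blinding, section {17a} says that "it is not possible to blind the study participants (children and teachers) to their condition (control/intervention"). The lead researcher, who collects the data, is blinded pragmatically, and the section admits that this is imperfect. By contrast, "Data analysts/video coders will be blind to condition (control/intervention) and time point (pre- or post-intervention") of each recording.

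The material for a blinded count is collected: "Flavour Explorers sessions will be video recorded, with an individual video stream for each child". What the coders are described as adding to WTT is one Gusto rating per child, from 1 to 5, multiplied by the card proportion. Both the unweighted and the weighted score will be reported.

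**The concern.** A face on the card serves as evidence that a food was licked, nibbled or eaten. If the arms differ after the intervention in how completely or accurately children mark their cards, the count differs even when tasting does not. Section {11a} says that intervention children spend a term on sensory food activities and learn to describe and share what they sense. That is close to what the card asks of them, so a change in marking is plausible.

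Baseline adjustment deals with a child's stable marking habit. It does not deal with a change in habit that the intervention itself brings about. Such a change would enter the self-reported score, the Gusto-weighted score and the composite of the primary measures. Meanwhile the observers who are blind to both arm and time point, and who already watch each child, have no described role in the count.

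**Working it through.** **1. Where each part of WTT comes from**

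| Part | Source | Blinding |
|---|---|---|
| Food marked or left blank | Child's card | Child not blinded |
| Supervision of the session | Researcher, with three or four children at one table | Pragmatic, imperfect |
| Scoring of the card | Lead researcher | Pragmatic, until scoring is done |
| Gusto, 1 to 5 | Video coders | Blind to arm and time point |

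The article gives no rule for correcting a card against what was seen.

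**2. What Gusto does to a wrong mark.** One wrong mark moves the self-reported score by 1/9 = 0.11. It moves the weighted score by Gusto/9, which is 0.11 at Gusto 1, 0.33 at Gusto 3 and 0.56 at Gusto 5. Because Gusto cannot fall below 1, the error is scaled and never removed. A single rating per child also cannot show which mark was wrong.

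**3. The planning figure, reproduced.** Section {14} gives a difference of 0.5 foods, SD 1.38, 90% power and 160 per arm. It states no significance level; I assume two-sided 5%. Then n = 2 × [1.38 × (1.960 + 1.282) / 0.5]² = 160.08, which matches. A one-sided 5% test gives 131, which does not.

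**4. Illustrative marking differences with equal tasting.** If 1 in 5 children in one arm mark one food more than they tasted, and none in the other arm do, the means differ by 0.2 × 1 = 0.2 food. That is 0.2/0.5 = 40% of the planning difference.

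Let b be the difference in marking. SE = 1.38 × √(2/n), which is 0.154 for n = 160 and 0.138 for n = 200 (400 children in two arms). The chance of significance is Φ(b/SE − 1.96) + Φ(−b/SE − 1.96).

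| b (foods) | 160 per arm | 200 per arm |
|---|---|---|
| 0.1 | 10% | 11% |
| 0.2 | 25% | 31% |
| 0.3 | 49% | 59% |
| 0.5 | 90% | 95% |

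Clustering and baseline adjustment are ignored here.

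**5. How much mis-marking would be needed.** The pilot section reports about 77% of children tasting 7–9 foods, about 20% tasting 1–6 and about 2% tasting none. With band midpoints, as an assumption, the mean is (0.77 × 8 + 0.20 × 3.5 + 0.02 × 0)/0.99 = 6.9 foods tasted, so 2.1 are not. A spurious 0.5-food difference needs one of these:
- 0.5/6.93 = 7% more of the tasted foods left unmarked in one arm than in the other (6–9% over the band limits)
- 0.5/2.07 = 24% more of the untasted foods falsely marked in one arm than in the other (15–63%)

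**The case against.** Several safeguards are real. The self-report is supervised at a small table, and the supervising researcher does not hold the allocation until the cards are scored. Gusto comes from blinded coders and may dampen false marks if a reluctant child is rated low. Both versions of WTT are reported. These reduce the risk, but each version still contains the card count, and one adult watching up to four children has no stated rule for a card that looks wrong.

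The coding regime is in Additional file 1, Appendix 2, which is not shown, and a video check may be described there. That stands as a limit on this point, although sections {17b} and {18a} both tie WTT to the card.

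Four stronger readings are tempting, and the documents do not support them.

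- **That illegible drawings make the count unreliable.** The protocol reports that "In pilots, the faces children drew were not always decipherable", but this is about which face was drawn, which matters for Liking. WTT needs only a mark or a blank.
- **That a false effect would arise, and in favour of the intervention.** Nothing in the documents gives the size or direction of a marking difference. Children trained to describe what they sense might equally make fewer false marks. Only *could* is supported.
- **That the plan contradicts itself.** Section {8} says "Outcomes measurement will focus on video recorded behavioural observation of children engaging in a tasting activity". A focus on video does not exclude a card, and the measure is openly labelled self-report.
- **That the card must be replaced outright.** The article does not show that every food can be identified on camera, so replacing the primary measure is debatable.

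**Conclusion.** The point holds in this form. The tasting count rests only on marks made by unblinded children, under supervision by an imperfectly blinded researcher. The blinded Gusto rating scales that count and cannot repair it. A change in marking caused by the intervention could be read as a change in tasting.

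The figures show sensitivity and are not an estimate of bias. They assume two-sided 5% testing and independent children. They also borrow an SD and a target difference from a four-food test in children aged 1–3 years, which may not carry over to a nine-food tray. On those terms a 0.2-food marking difference is 40% of the planned effect and significant about one time in four. This does not invalidate the design, but a primary outcome deserves the blinded check that the recordings may allow at little cost.

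**What to change.** In the existing annotation pass, have the blinded coders press a key for each new food that is licked, nibbled or eaten. They already log sensory words this way. Then:

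1. Prespecify an analysis of WTT, and of WTT × Gusto, with the video count divided by nine, alongside the card-based result.
2. Keep the two sources apart within a score. Where footage does not show a taste, do not fill the gap from the card; report how often this happens, by arm and time point.
3. Report card–video agreement by arm and by time point.
4. State that a conclusion about tasting must also hold on the blinded count where tastes are visible.

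If Appendix 2 already contains such a log, state it in the outcome definition and add items 1 to 4.

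The cost is one more key code, normally at most nine presses per session, and slightly longer coding. Data collection does not change. The drawback is that some tastes will be out of view or hard to tell from a repeat taste, so the video count may miss some. Item 3 shows whether those misses differ between arms.
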